#### Giving outcomes a value

In the final part of this process, we give the identified outcomes a monetary value using financial proxies that reflect that importance of the outcome to stakeholders (see Table 3). In consultation with the YAC, a sense of connectedness and sense of belonging was considered similar to having friends. Powedthavee (64) identified the economic value of making and having new friends, in addition to existing friends, and this value was subsequently updated and converted to Australian dollars (See Table 3). Given that the original value was calculated in 2007, we adjusted it for inflation to reflect its current purchasing power, ensuring consistency with contemporary economic conditions. Although using a currency converter may not be the ideal method, this approach, when combined with inflation adjustments, provides a reasonable approximation of the value in today’s terms.

**Table 3 tab3:** SROI stage 3 outcomes.

Stakeholder		Stage 3				
Satellite young person participants		The outcomes (what changes)				
	Outcome	How will we know if the outcome has occurred	Source	How can you value the change?	Value $AUD for six-month period	Source
		Measured how?	Where this information comes from	What proxy is used to value the change?	Value of the change	Where this information comes from
	Sense of belonging and increased connectedness	Feel more connected to other young people living in similar circumstances	SDQ: Prosocial behaviour subscale (child and parent versions) LSAC items on connectedness Interviews with children/youth	Powdthavee (64) identified the economic value of friends (in addition to existing friends): 15,500 pounds per year in 2007 is equivalent to 23,903.38 pounds in 2022, converted to 2022 AUD 42,818.76 *per annum*	$21,861.38	Powdthavee (64).
		Reduced feelings of isolation and increased feelings of belonging				
	Increased resilience	Decreased mental health crises	CYRM-R total score KCS, completed by children aged 10 years and under; CASQ, completed by older children, adolescents and young adults Interviews with children/youth	The Australian Psychological Society (APS) recommends $300 per hour per child/young person for psychological services – 14 sessions	$4,200 per child/young person	APS website: https://psychology.org.au/psychology/about-psychology/what-it-costs

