	Sense of hope, optimism and possibility	Increased hope for the future that results in planning for future activities/goals, agency	Children’s Hope Scale Interviews with children/youth	Cost of a mentor such as what might be available from the Big Brothers, Big Sisters mentoring program: $2,500 per person for 12 months	$1,250	Big Brother, Big Sisters of Australia Annual Report 2019–2020 BBBS_Annual_Report_2019-2020.pdf (bigbrothersbigsisters.org.au)

We also identified a financial proxy for resilience. For the young people involved in these programs, resilience refers to achieving positive outcomes (inclusive of wellbeing) despite coming from challenging backgrounds, and adaptively coping with current stressors (see Figure 1, Theory of Change). According to Olsson et al. (48), promoting resilience at an individual level involves developing personal coping skills and resources, both of which they suggest may be obtained from one to one therapy. Pascual-Leone et al. (49) suggested 14 individual sessions is appropriate for individuals with existing issues. It was on this basis that resilience was valued as 14 individual, psychotherapeutic sessions (see Table 3). The assumption that 14 individual psychotherapeutic sessions has a similar effect to a one-day workshop (e.g., the Create and Connect program) is admittedly contestable. However, a one-day workshop that focuses on creativity and connectedness can offer an intensive, immersive experience that might be considered similar to the impact of multiple counselling sessions (33, 50). Moreover, the unique therapeutic mechanisms of creative programs can lead to profound insights and emotional processing (51–53), potentially achieving in 1 day what might take multiple counselling sessions. The added dimension of group dynamics in these programs which emphasises peer support, can amplify the overall therapeutic impact (33, 50, 51), again potentially contributing to outcomes comparable to multiple individual counselling sessions.

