## Calculating the SROI

Calculating the SROI involves adding up the outcomes (value), applying the discounts (attribution, displacement, deadweight and drop off) and comparing the result to the investment or costs incurred in delivering the program. Costs involved for Satellite involve employing staff to facilitate programs (including administration and registration), insurance, venue hire, catering, materials and travel (Satellite sometimes pays for transport so that young people/children can attend programs). Expenses associated with reimbursing YAC members for their input and advice on the programs offered is also included. Our analysis spanned a six -month period only (as indicated in Table 3), which does not necessitate the use of a discount rate to account for the time value of money (58). As the timeframe is less than a year, no additional adjustments for the differing value of money over time were required.

Once the net present value of costs and outcomes have been established (taking into consideration drop off, deadweight and displacement), the final ratio can be calculated. The formula for calculating the return on investment is:

SROI ratio = Social value of stakeholder outcomes (discounted)

Cost of providing programs

According to Arvidson et al. (23), an SROI ratio greater than one indicates a positive return on investment, or in other words, where the benefits of the investment are greater than its costs. The calculation is based on proxy values, as outlined in Table 3.

As the results are influenced by non-quantitative variables and assumptions, a sensitivity analysis for the SROI will be calculated to promote robustness. After establishing a base case scenario as outlined above, each key assumption will be changed (by ±10%), one at a time, to ascertain how much the SROI ratio changes. Changes in the SROI will be compared for each variation and those assumptions that cause the most significant changes in the SROI ratio identified. Several plausible scenarios will be developed including best case, worse case and moderate scenarios, using most optimistic to most pessimistic values of each of the assumptions. Each of these scenarios will be reported including a discussion of which assumptions have the most significant impact on the SROI ratio.

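### The annual and six-month friendship values in Table 3 disagree by AUD 452.00, and the largest SROI proxy must be reconciled before the ratio is calculated

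*Protocol article*

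**What the plan says.** Under Giving outcomes a value, Table 3 assigns a financial proxy to each of three outcomes. The value column is headed "Value $AUD for six-month period".

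- **Belonging and connectedness.** The annual basis is a cited study's value of additional friends: "15,500 pounds per year in 2007 is equivalent to 23,903.38 pounds in 2022, converted to 2022 AUD 42,818.76" per annum. The six-month cell is AUD 21,861.38.
- **Resilience.** 14 psychology sessions at AUD 300 each, entered as AUD 4,200.
- **Hope, optimism and possibility.** A mentoring cost of AUD "2,500 per person for 12 months", entered as AUD 1,250.

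The section Calculating the SROI ties the time frame to the same table ("Our analysis spanned a six -month period only (as indicated in Table 3"). It says of the time value of money that "no additional adjustments for the differing value of money over time were required", and of the ratio itself: "The calculation is based on proxy values, as outlined in Table 3".

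**The concern.** The friendship row prints an annual value and a six-month value, both to the cent, and the second is not half of the first. A reader who tries to rebuild the largest proxy from the figures given cannot do so.

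The friendship value is about 80% of the sum of the three proxies, so whichever figure goes into the calculation largely sets the numerator. The article lists transparency and the avoidance of overclaiming among its guiding principles, and its Conclusion expects the findings may be used to lobby for funding. An unexplained discrepancy in the main input sits badly with both. The planned sensitivity analysis moves assumptions around a base case. It does not repair a base case that starts from the wrong figure.

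**Working it through.** **Inputs**, all from Table 3: annual friendship value GBP 15,500 (2007), GBP 23,903.38 (2022) and AUD 42,818.76 (2022); six-month friendship value AUD 21,861.38; resilience 14 sessions at AUD 300; mentoring AUD 2,500 for 12 months.

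**Step 1: the rows that reproduce.**
- Resilience: 14 × 300 = 4,200, as printed.
- Mentoring: 2,500 / 2 = 1,250, as printed. The column's rule for an annual figure is therefore a plain halving.

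**Step 2: the friendship row.**
- 42,818.76 / 2 = 21,409.38; printed 21,861.38.
- Difference: 21,861.38 − 21,409.38 = 452.00.
- Relative size: 452.00 / 21,409.38 = 2.11%.

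**Step 3: could another half-year convention give the printed cell?**
- 26/52 weeks: 21,409.38.
- 183/365 days: 42,818.76 × 183/365 = 21,468.04.
- 184/365 days: 42,818.76 × 184/365 = 21,585.35.
- The printed cell would need 21,861.38 / 42,818.76 × 365 = 186.4 days, or 6.13 months.

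None fits, and the article describes no further adjustment.

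**Step 4: the same check from the other side.**
- 2 × 21,861.38 = 43,722.76, which is 904.00 above the printed annual value.
- Exchange rate implied by the printed annual value: 42,818.76 / 23,903.38 = 1.7913 AUD per pound.
- Exchange rate implied by the six-month cell: 43,722.76 / 23,903.38 = 1.8291 AUD per pound.

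The article states no rate, so neither can be preferred from the text.

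**Step 5: weight in the numerator**, assuming every outcome is credited to the same number of participants with the same deductions.

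| | Six-month cell as printed | Half of printed annual value |
|---|---|---|
| Friendship | 21,861.38 | 21,409.38 |
| Resilience | 4,200.00 | 4,200.00 |
| Hope | 1,250.00 | 1,250.00 |
| Sum | 27,311.38 | 26,859.38 |
| Friendship share | 80.0% | 79.7% |

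Difference in the sums: 452.00 / 26,859.38 = 1.68%.

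**The case against.** Nobody can fairly dispute that the two figures disagree: both are complete and sit in their proper cells, and nothing elsewhere in the article corrects them. The serious objections concern what follows.

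*Direction.* A reader might infer that the six-month proxy is overstated and that the ratio will be biased upwards. That takes the annual AUD figure as correct, which the article does not establish. If the annual figure is the slip, AUD 43,722.76 halves exactly to the printed cell and nothing in the value column is too high. This objection stands.

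*Size.* The 80% share and the 1.7% depend on equal counts and deductions. Under Deadweight and displacement, the LSAC comparison serves connectedness only, with interviews used for the other outcomes, so deductions may well differ. The discrepancy is also about a fifth of the planned ±10% one-way variation. This stands as a limit on the effect. It does not excuse an inconsistent base-case input.

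*No ratio yet.* The article describes a forecast SROI with data still being collected and reports no ratio. Which figure the working calculation holds is unknown. This also stands: the risk is to a result still to come.

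*Price years.* A reader might add that friendship is in 2022 AUD, that the mentoring cost comes from a 2019–2020 report with no stated uplift, and that the SROI period runs from January 2023 to mid-2024. That is a separate matter. Its size needs a price index the article does not give, and if prices rose, a common later price year would raise the proxies. It lends no support to a claim of overstatement.

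**Conclusion.** The point holds as an internal inconsistency. The annual and six-month friendship values in Table 3 cannot both be right: they differ by AUD 452.00 at six months per credited participant, or 2.11% of the proxy. That result is exact and rests only on the printed figures and the column's own halving rule.

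The effect on the ratio is conditional. If the annual value is right and the printed cell is used, the sum of the three proxies is 1.7% too high under equal counts and deductions. If the six-month value is right, the value column needs no change and only the stated derivation is wrong. The document does not allow a choice between these, so an upward bias is not demonstrated. The discrepancy is small and on its own would alter a reading against the threshold of one only for a ratio very close to one. It still needs correcting, because it lies in the largest input to the calculation.

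**What to change.** Check both friendship figures against the inflation and currency conversion that produced them, and state the exchange rate and its date in Table 3. Then correct whichever figure is wrong:

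- if AUD 42,818.76 per annum stands, enter AUD 21,409.38 as the six-month value;
- if AUD 21,861.38 for six months stands, correct the annual value to AUD 43,722.76.

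Use the reconciled figure in the SROI base case, and so in the sensitivity and scenario analyses built on it. The cost is one table cell, a sentence on the conversion and a check of the calculation file. No new data are needed. The ratio falls slightly in the first case if the printed cell was in use, and is unchanged in the second if the printed cell was already in use. Any move to a common price year should be decided and documented separately.

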## Establishing impact

This step examines aspects of change that would have happened anyway or are a result of other factors, both of which need to be considered and eliminated. There are four parts to this stage as outlined below.

### Deadweight and displacement

Deadweight identifies changes in participant circumstances or resources that might have occurred regardless of whether the program or activity had taken place. One of ways we will calculate deadweight, is be using data from the Longitudinal Study of Australian Children (LSAC) survey, as a benchmark or comparison group of young people not involved in Satellite’s programs. The LSAC includes a group of Australian children/adolescents who have self-identified as having caring responsibilities (56). These will be matched with some of the young people who have participated in Satellite’s programs on demographic variables of age, gender and socio-economic status. Commencing in 2003, the LSAC is a national longitudinal study of data collected every 2 years on various child, parental and family characteristics that influence children’s development at different ages (56). Specific LSAC items will be used, as pertaining to connectedness /belonging outcomes, though noting that comparative data are only available for young people aged 14 years and above. This means that only some of the Satellite group will be included, and only on the connectedness outcome, with children under 13 years of age not being compared to the LSAC group and other outcomes not being compared. It is possible that one or more young people from the LSAC cohort may have attended a Satellite program. Given that Satellite is a unique program only available to young carers living in Victoria (while LSAC is an Australian cohort), and the level of help-seeking within this cohort will be variable (collected as frequency data, not details of programs), the likelihood is considered small within the Victorian LSAC participants and unlikely for those residing interstate.

An *a priori* power analysis was conducted using G*Power version 3.1.9.7 software (65) to determine the minimum sample size required for the study. The required sample size to achieve 80% power for detecting a medium effect at a significance criterion of *α* = 0.05 will be 29 per group {intervention [Satellite participants] and usual care [LSAC]; as per (30)}. Other deadweight measures will be ascertained by asking young people what they perceive would have happened if they had not attended Satellite and their estimation of the impact of that occurrence (in the interviews). This is necessary as there is a risk that LSAC participants may be engaged in programs similar to Satellite. Their responses will be used to inform and qualify any differences between the LSAC calculations and the Satellite participant sample as well as deadweight across other age groups and for other outcome measures not included in the LSAC data set.

Displacement is an assessment of how much the outcome might have displaced other outcomes, including the occurrence of negative outcomes for the children and young people and others. An evaluation of a similar program {Paying Attention to Self [PATS]; (57)} found that building new connections with participants during the program came at the cost of building peer relationships in other sites outside the program such as school and this is a concern that could apply here. Alternatively, participants could be gaining transferrable social skills at Satellite that then lead to better connections at school and other settings. We will be investigating this and other potential outcomes in the conversations with young people and who they are turning to.

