## Abstract

The purpose of this paper is to describe the protocol for the evaluation of programs offered by the Satellite Foundation, designed for, and with, children and young people aged between 8 and 25 years who have family members experiencing mental health challenges. To achieve this, the Social Return on Investment (SROI) method was chosen. SROI is an economic measurement tool used to apply a monetary value to socially situated outcomes. In this study, SROI will be used to provide a means of quantifying the social impact generated by various programs offered by the Satellite Foundation, a community-based mental health organisation. These programs are designed for children and young people who have a family member who experiences mental health challenges, with the aim to promote resilience, hope and connectedness. Given that traditional financial metrics often fail to capture societal benefits, SROI offers a systematic approach to measuring the economic and often intangible social outcomes of any given endeavour. This protocol will describe the SROI method, who the stakeholders are, and how they are engaged. The rationale for the monetisation of outcomes is shown. Other SROI steps are presented, including how impact was established, and the proposed method of calculating the SROI. The limitations and potential benefits of this economic measurement approach are also discussed.

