## Introduction

Family systems theory posits that the health of one member of a family can have a profound impact on the well-being of other family members (1). Likewise, young people who have a parent, sibling or other family member who experiences mental health challenges confront complex issues that can influence their own mental health, developmental and/or behavioural outcomes. Many of these young people assume caring responsibilities in their families (2), a role which can provide young people a sense of purpose and strengthen family bonds, but if onerous, can adversely impact their wellbeing and friendship groups (3). Similarly, while many children and young people in these families identify independence and compassion as positive outcomes (4), others report negative outcomes including low academic attainment (2, 5) and their own mental health and adjustment issues (6). These young people are often considered to be “invisible” as services focus on the needs of their family member and typically do not intervene with children unless there is evidence of abuse or neglect (7). However, there is much that can be done to mitigate these potential negative impacts, if given the necessary support.

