The purpose of this paper is to describe the SROI protocol for the evaluation of programs designed for, and with, children and young people aged 8–25 years, and who have family members (parents/guardians and/or siblings) who experience mental health challenges. The programs are offered by the Satellite Foundation (hereafter Satellite), an Australian not-for-profit organisation. Satellite provides various in-person and online programs for these children and young people, with the aim of promoting connectedness, wellbeing, and resilience. Programs vary in *length*, *approach* (for example some involve creative activities, others are more psychoeducational) and *medium* (online and face-to-face) and target different *age* groups. Participants can choose any number of programs to join and may participate in multiple programs. While it is acknowledged that the three identified programs have varying lengths, approaches and mediums, they share the same Theory of Change (Figure 1). As Arvidson et al. (23) argued, a consistent Theory of Change allows for a structured approach for evaluating outcomes across different programs. Moreover, the mixed method approach employed ensures that the nuances of each program are captured while maintaining a consistent framework for evaluation (26). Satellite actively promotes and encourages young people to stay engaged via their connecting procedures where they maintain contact between programs. The SROI for Satellite is part of a larger evaluation currently underway (30).

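### The LSAC comparator for deadweight is not selected or matched on family mental illness, so connectedness deadweight for participants aged 14 and over is open to confounding that the article does not acknowledge

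*Protocol article*

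**What the plan says.** The Abstract describes the programs as being for "children and young people aged between 8 and 25 years who have family members experiencing mental health challenges". The Social Return on Investment approach section repeats the definition: participants are those "who have family members (parents/guardians and/or siblings) who experience mental health challenges". The Introduction says that a relative's mental health challenges can affect the young person's own mental health, development and behaviour. On caring, it says: "Many of these young people assume caring responsibilities in their families".

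The Deadweight and displacement section defines the comparator differently. It takes LSAC children and adolescents "who have self-identified as having caring responsibilities" and matches them to some Satellite participants "on demographic variables of age, gender and socio-economic status". The same section says LSAC collects "various child, parental and family characteristics that influence children’s development at different ages", but apart from socio-economic status it names none of these for matching. The comparison is confined to connectedness, because "comparative data are only available for young people aged 14 years and above".

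LSAC is presented as one source of deadweight among several. A second source is interviews, "asking young people what they perceive would have happened if they had not attended Satellite". The reason given for the interviews is that LSAC members may be attending similar programs.

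**The concern.** Deadweight is the deduction for change that would have happened without the program. A comparison group supplies it correctly only if its connectedness would have moved as the participants' would have, absent Satellite. Here the groups are selected on different characteristics: one on a relative's mental illness, the other on caring, with no condition on why care is given. A young person caring for a relative with a physical illness would qualify as an LSAC comparator.

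The article itself treats family mental illness as something that shapes these young people's outcomes. Age, gender and socio-economic status do not stand in for it. If connectedness follows a different course in the two groups, the deduction will be too large or too small. The outcome affected has by far the largest proxy value in Table 3.

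**Working it through.** **Group definitions side by side**

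| | Satellite participants | LSAC comparators |
|---|---|---|
| Defining feature | Relative with mental health challenges | Self-identified caring responsibilities |
| Family mental illness | Present by definition | No condition stated |
| Caring role | Many, per the Introduction; other sections call them young carers | Present by definition |
| Matched on | Age, gender, socio-economic status | Same |
| Ages compared | 14 and over | 14 and over |

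The row on family mental illness is where the groups differ, and nothing in the stated matching closes the gap.

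**Weight of the outcome.** Table 3 gives six-month proxies of AUD 21,861.38 (connectedness), 4,200 (resilience) and 1,250 (hope).

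- Sum: 21,861.38 + 4,200 + 1,250 = 27,311.38
- Connectedness share: 21,861.38 / 27,311.38 = 80.0%

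Half of the annual 42,818.76 shown in Table 3 is 21,409.38, slightly below the tabulated six-month value. Using it gives 21,409.38 / 26,859.38 = 79.7%, so the share hardly depends on which figure is used.

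**Effect of an error in deadweight.** The article gives no deadweight figure to reproduce, so the values below are assumptions. Write net connectedness value as proxy × (1 − d), where d is true deadweight. An error of e changes it by e / (1 − d). If the other outcomes have the same true d, total value changes by 0.800 × e / (1 − d).

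| d (assumed) | e (assumed) | Net connectedness | Total value |
|---|---|---|---|
| 20% | 10 points | 0.10/0.80 = 12.5% | 10.0% |
| 20% | 20 points | 0.20/0.80 = 25.0% | 20.0% |
| 30% | 10 points | 0.10/0.70 = 14.3% | 11.4% |
| 30% | 20 points | 0.20/0.70 = 28.6% | 22.9% |
| 40% | 10 points | 0.10/0.60 = 16.7% | 13.3% |
| 40% | 20 points | 0.20/0.60 = 33.3% | 26.7% |

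The sign can go either way. The table applies the error to everyone. If LSAC deadweight is used only from age 14, multiply the last column by the share of connectedness value arising in that age group. With half (assumption), the 30% rows become 5.7% and 11.4%.

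**Reach of the planned sensitivity analysis.** Calculating the SROI varies each key assumption by ±10%, one at a time. Read as a relative change, a 30% deadweight (assumed) moves only between 27% and 33%. That is 0.03/0.70 = 4.3% of net connectedness value and 0.800 × 4.3% = 3.4% of the total, well inside the illustrated error.

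**The case against.** Much can be said for the plan.

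- **Participants as carers.** A reader might infer that Satellite participants need not be carers and that the groups therefore differ in both directions. The text is mixed. The Introduction says only that many are carers, but the Deadweight section describes Satellite as open to young carers in Victoria, and the scope section and Table 1 use similar language. That half of the mismatch is weak. The other half stands: LSAC carers need not have mental illness in the family.
- **Level versus change.** Deadweight concerns change. A stable difference in level would not by itself distort a comparison of changes; a different natural course is needed, and the documents give none. This rules out saying that bias has been shown, but leaves the risk in place.
- **Other sources and scenarios.** LSAC is only one deadweight source, interviews qualify it, and best, worst and moderate scenarios are planned. These soften the problem. However, the interviews record perceived counterfactuals and are justified by similar programs, not by a different population. No scenario range is tied to this mismatch.
- **Coverage.** Two of the three programs start at age 8, so part of the sample never meets the LSAC comparison. This reduces the size.
- **Unseen evaluation protocol.** The cited evaluation protocol may define the LSAC group more narrowly. This article nevertheless states both the definition and the matching variables without qualification.

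The Limitations regret the lack of a comparison group for under-14s and for other outcomes. They do not say that the group that was found comes from a differently defined population.

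**Conclusion.** The point holds as a risk of confounding. The comparator is neither restricted to, nor matched on, the exposure that defines the participants, and the article does not say so. It affects LSAC-based deadweight for connectedness at age 14 and over.

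Two stronger readings are not supported. A reader might infer that the deadweight is biased in a known direction; the documents give neither direction nor size. A reader might also take 11 to 23% as the expected error in total value. That range is an upper illustration: it assumes 30% deadweight, an error of 10 to 20 points, LSAC deadweight applied to every participant, and no correction from the interviews. The 80.0% is likewise a share of per-person proxy values. The share of realised value will depend on how many participants achieve each outcome.

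It is worth acting on because the change fits a matching step that is already planned.

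**What to change.** In the planned matching, or in a regression adjustment:

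1. Restrict to, match on or adjust for an LSAC parental or family mental-health variable, if LSAC holds one. The article mentions parental and family characteristics but does not confirm this one.
2. Adjust for prior connectedness where an earlier LSAC wave at age 14 or over carries the same items. Waves are two years apart and comparative data start at 14, so a comparator generally has to be at least 16 at the later wave (14 + 2). A score two years old is also not the same as Satellite's entry score six months before follow-up, and the report should say so.
3. If these variables are not held, state in the Limitations that the LSAC group is a different population. Give connectedness deadweight a range wider than ±10% in the planned scenarios to reflect this.

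This is a cheap improvement. Items 1 and 2 shrink the pool of eligible LSAC matches, so it should be checked against the stated 29 per group before the rule is fixed. Item 3 costs a sentence and one scenario range.
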